**Table 2 schedule of data collection**

|                                                      | Screening for Enrollment | Standard DAPT and randomization | After randomization       |
|------------------------------------------------------|--------------------------|---------------------------------|---------------------------|
| Study procedures                                     | After PCI                | Until 6 months after PCI        | Until 12 months after PCI |
| Follow-Up                                            | Visit 1                  | Visit 2                         | Visit 3                   |
| Window Period                                        | 0-7 days                 | ±7 days                         | ±14 days                  |
| Eligibility Criteria                                 | X                        |                                 |                           |
| Patient Informed Consent                             | X                        |                                 |                           |
| Withdrawal                                           | X                        | X                               | X                         |
| Medical History/ Demographics                        | X                        |                                 |                           |
| Previous Medical History                             | X                        |                                 |                           |
| Vital Signs                                          | X                        | X                               | X                         |
| Height and Weight                                    | X                        |                                 |                           |
| Physical Examination                                 | X                        |                                 |                           |
| Cardiac Markers (including TnT or TNI/CK/CK-MB)      | X                        |                                 |                           |
| Blood Routine Test 
(RBC/WBC/HGB/PLT) | X                        | X                               | X                         |

|                                                                                        |   |   |   |
|----------------------------------------------------------------------------------------|---|---|---|
| Coagulation Function Test (PT/APTT/FIB)                                                | X |   |   |
| Fecal Occult Blood Test                                                    | X | X | X |
| Platelet Aggregation Test  (light transmission aggregometry and VerifyNow) | X | X | X |
| HP Breath Test                                                                         | X |   |   |
| 12-Leads ECG                                                                           | X |   |   |
| AMCE Examination                                                                       | X | X | X |
| Drug Distribution/Recycling                                                            | X | X | X |
| Concomitant Medications                                                                | X | X | X |
| Adverse Events                                                                         | X | X | X |

1: one time per two months; 2: 34 patients per group in the principal research site

6-month visit: Each enrolled subject will be followed with an in-clinic face-to-face visit at 6 months after enrollment. Screening should be conducted before the 6-month face-to-face visit, subjects who are not eligible for randomization will not be required to complete the 6-month face-to-face visit.

12-month visit: Randomized subjects will return for the final in-clinic additional in-clinic face-to-face visits at 12 months after enrollment. Vital status of subjects who did not meet eligibility for randomization can be obtained from medical records or public records at 12 months after enrollment.

### 3.6.1 Study timetable and end of study

Trial enrolment in OPT-PEACE began in July 2017 with the last patient enrolled on July 2019. The last patient follow-up visit will occur in Jun. 2020.

## 4 Primary and secondary variables

### 4.1 Primary variable

The primary endpoint is the incidence of gastric or intestinal mucosal injury occurring within 12 months after enrollment, defined as erosion, ulceration or bleeding detected by either planned AMCE or clinically-driven endoscopy. Specifically, gastrointestinal erosion is defined as superficial mucosal breaks with a diameter of  $<5$  mm.

Gastrointestinal ulcer is defined as a mucosal break with a diameter  $\geq 5$  mm, typically covered with fibrin.

Situations below can be regarded as valid primary endpoint results, including:

- Successful completion of the AMCE examination at 6 months after randomization (i.e., 12 months after enrollment), regardless of the results of examination;
- Although the third AMCE examination at 6 months after randomization is not done, the second examination at 6 months after PCI reports new-onset gastric or small intestinal mucosal lesions;
- AMCE or gastroscopy examination driven by the occurrence of gastrointestinal bleeding at any time during the whole study period observes new-onset gastric or small intestinal mucosal lesions.

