## **11. EVALUATION AND CALCULATION OF VARIABLES**

### **11.1 Primary Endpoint**

The primary endpoint of this study is the gastric and small intestinal mucosal injury (a composite of erosion, ulceration or bleeding) occurring within 12 months after enrollment.

Situations below can be regarded as valid primary endpoint results, including:

- Successful completion of the AMCE examination at 6 months after randomization (i.e., 12 months after enrollment), regardless of the results of examination;
- AMCE or gastroscopy examination driven by the occurrence of gastrointestinal bleeding at any time during the whole study period observes

new-onset gastric or small intestinal mucosal lesions.

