## **5 Sample size**

The cumulative incidence of the primary endpoint of gastric or intestinal mucosal lesions within 12 months is estimated to be 47% in patients who received 12 months of DAPT and 30% in those treated with either aspirin or clopidogrel monotherapy beginning at 6 months after enrollment. With a 2:1 ratio in patients treated with either aspirin or clopidogrel monotherapy after 6-month DAPT versus DAPT for 12 months, 384 evaluable patients (256 and 128 respectively) provide 90% power to detect a 17% absolute risk reduction (36% relative risk reduction) with a 2-sided type I error of 0.05. Assuming 20% loss of evaluable primary endpoint outcome assessments due to patient withdrawal, loss to follow-up between 6 and 12 months or suboptimal AMCE visualization of the GI tract at 12 months, 480 patients are planned to be randomized. Assuming that an additional 10% of enrolled patients will not be randomized at 6 months because of adverse clinical events, noncompliance with antiplatelet therapy or lost to follow-up or withdrawal, 534 patients were initially planned to be enrolled after baseline screening. Finally, assuming that 10% of patients who undergo a screening AMCE examination will be excluded due to gastrointestinal ulcer or bleeding, approximately 593 patients were initially planned to be consented and undergo the screening AMCE examination.

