## **6 Analysis sets**

### **6.1 Full analysis set (FAS)**

All patients who have been randomized to study treatment will be included irrespective of their protocol adherence and continued participation in the study. Patients will be analysed according to their randomized study drug assignment (not to which treatment they actually received) irrespective of whether the event occurred before or following discontinuation of study drug. Patients who withdraw consent to participate in the study (or are lost to follow-up) will be included up to the date of

their study termination except for vital status known through public records (for use in the analyses of deaths). All primary, secondary, and exploratory efficacy variables will be analyzed using the FAS. The primary endpoint of gastric or intestinal mucosal injury will be analyzed in a modified intention to treat (mITT) population, (i.e., patients with valid primary endpoint results). Unless otherwise stated, the FAS will be considered the primary analysis set for the primary and secondary variables and for the exploratory variables.

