## **8 Lost to follow-up and missing data**

In keeping with an intent-to-treat philosophy, the primary analyses are performed on all randomized subjects. We anticipate that the amount of missing data will be minimal in the present study as we are specifically asking sites to ensure that the data elements are complete. No imputation will be carried out for missing baseline data.

If outcome data are missing, to assess the potential impact of missing data, a sensitivity analysis will be conducted which will include a complete case (including only subjects whose AMCE outcome is known at 6 months after randomization), a best-case (assume missing subjects in monotherapy group are event free at 6 months and missing subjects in DAPT have gastric or intestinal mucosal injury at 6 months), a worst-case (assume missing subjects in monotherapy group have gastric or intestinal mucosal injury at 6 months and missing subjects in DAPT group are event free at 6 months), and a tipping point analysis if the conclusion is changed in the worst-case analysis.

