### 9.2 Analysis for the primary endpoint

The primary objective of OPT-PEACE trial is to determine the impact of 6-month DAPT plus 6-month single antiplatelet therapy versus 12-month DAPT in terms of the primary endpoint (gastrointestinal injury) after contemporary DES implantation. This analysis will be carried out in the FAS. The null hypothesis ( $H_0$ ) for this analysis is that the incidence of primary endpoint in the experimental group is same as that of the control group, namely  $P_0=P_1$ . The alternative hypothesis ( $H_1$ ) is that the incidences of primary endpoints in the two groups was not equal, namely  $P_0 \neq P_1$ , and the superiority test is conducted at the 2-sided significance level of 0.05. An odds ratio (OR) and two-sided 95% CI for the primary endpoint will be generated using the logistic regression model with treatment (monotherapy group vs. DAPT group) as fixed effect factors. This analysis will be repeated in the PPS to support the main results.

In addition, for the purpose of exploration, primary endpoint will also be compared across the 3 groups, and for all single group versus group comparisons (12-month DAPT vs 6-month DAPT plus 6-month aspirin monotherapy; 12-month DAPT vs 6-month DAPT plus 6-month clopidogrel monotherapy; and 6-month DAPT plus 6-month aspirin monotherapy versus 6-month DAPT plus 6-month clopidogrel monotherapy).

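### Among randomised patients without a 12-month capsule exam, the SAP counts only those with a positive earlier or bleeding-driven exam and drops those with a clean 6-month exam

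*Supplement*

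**What the plan says.** The primary endpoint (SAP 4.1) is gastric or intestinal erosion, ulceration or bleeding within 12 months of enrolment, so it includes the six months before randomisation. SAP 4.1 then lists three situations that give a valid primary result:

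1. A completed 12-month AMCE, whatever it shows. Protocol V1.4 section 11.1 words this as "Successful completion of the AMCE examination at 6 months after randomization (i.e., 12 months after enrollment), regardless of the results of examination".
2. No 12-month AMCE, but a positive earlier one: "Although the third AMCE examination at 6 months after randomization is not done, the second examination at 6 months after PCI reports new-onset". The finding meant is a mucosal lesion of the stomach or small bowel.
3. A positive bleeding-driven exam: "AMCE or gastroscopy examination driven by the occurrence of gastrointestinal bleeding at any time during the whole study period observes new-onset". The same kind of lesion is meant.

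Protocol 11.1 has the first and third routes but not the second.

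SAP 6.1 says the primary endpoint "will be analyzed in a modified intention to treat (mITT) population, (i.e., patients with valid primary endpoint results". SAP 9.2 says of the primary comparison, "This analysis will be carried out in the FAS", and SAP 8 says the primary analyses are on all randomised subjects.

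On missing outcomes, SAP 8 states "We anticipate that the amount of missing data will be minimal in the present study", while SAP 5 sizes the trial by "Assuming 20% loss of evaluable primary endpoint outcome assessments". SAP 8 plans complete-case, best-case and worst-case sensitivity analyses, and a tipping-point analysis if the worst case changes the conclusion.

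**The concern.** Take two randomised patients who both miss the 12-month AMCE and have no bleeding-driven exam. One had an erosion at 6 months: she enters the primary analysis as an event. The other had a clean 6-month exam: he has no valid result and is left out. The finding itself decides who is in the denominator, and among patients admitted by the second or third route the event proportion is 100% by construction.

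Under SAP 3.3, ulceration or bleeding on the 6-month AMCE bars randomisation, so events added by the second route are erosions seen before treatment was assigned. If equal shares of each arm lack the final exam, the rule adds the same proportion of events to both and dilutes the contrast. If the shares differ, it produces a difference that treatment did not cause. Because this sits in the definition of the primary analysis population, it affects the primary test.

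**Working it through.** **The plan's own figures.** Inputs from SAP 5: 47% DAPT, 30% monotherapy, 2:1 allocation, two-sided 5%, 90% power. The pooled-variance formula without continuity correction gives 127 DAPT and 381 in total, against the stated 384. With 128 and 256 evaluable patients, power is 90.3%. 384/0.8 = 480 randomised, that is 160 DAPT and 320 monotherapy. The design reproduces.

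**Effect of the rule.** Let p be the true 12-month cumulative rate, m the share without a 12-month AMCE and q the share of those with a 6-month erosion. Missingness is taken as unrelated to outcome within arm, and bleeding-driven exams are ignored. The analysed rate is

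[(1−m)p + mq] / [(1−m) + mq].

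SAP 5 supplies m = 20%. The documents do not give q; 15% to 25% is an assumption.

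| q | DAPT | Monotherapy | Difference | Patients added (all events) | Power |
|---|---|---|---|---|---|
| 15% | (0.376+0.03)/0.83 = 48.9% | (0.24+0.03)/0.83 = 32.5% | 16.4 points | 4.8 + 9.6 | 88.6% |
| 25% | (0.376+0.05)/0.85 = 50.1% | (0.24+0.05)/0.85 = 34.1% | 16.0 points | 8 + 16 | 87.5% |

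Patients added are 160mq and 320mq. Power falls although the analysed sample grows. With m equal across arms and no true effect, both arms shift alike and type I error stays at 5%.

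**Unequal missingness, no true effect.** Set p = 30% in both arms, with 25% missing on DAPT and 15% on monotherapy (an assumed imbalance).

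- q = 15%: (0.225+0.0375)/0.7875 = 33.3% against (0.255+0.0225)/0.8725 = 31.8%, a false +1.5 points.
- q = 25%: (0.225+0.0625)/0.8125 = 35.4% against (0.255+0.0375)/0.8875 = 33.0%, a false +2.4 points.

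Reversing the imbalance gives −1.5 and −2.4 points. Type I error is about 6% to 8% in these cases. A wider assumed gap of 30% versus 15%, with q from 10% to 30%, gives +1.7 to +4.5 points and type I error of about 6% to 14%.

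**Symmetric handling recovers the truth.** Among those without a third exam, keep the q observed events and give the 6-month-negative patients their expected later risk (p−q)/(1−q). At q = 25% this is 0.22/0.75 = 29.3% on DAPT and 0.05/0.75 = 6.7% on monotherapy. The rates in that group become 0.25 + 0.75×0.293 = 47% and 0.25 + 0.75×0.067 = 30%, the design values.

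**The planned worst case at 20% loss.** Patients with a 6-month erosion have a known outcome under SAP 4.1, so only the 6-month-negative ones are missing.

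- Monotherapy: 0.8×0.30 + 0.2 = 44.0%.
- DAPT: 0.8×0.47 + 0.2q = 40.6% (q = 15%) to 42.6% (q = 25%).
- Break-even: m = 0.17/(1.17−q) = 16.7% to 18.5%.

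So at the planned loss the worst case reverses the direction even when the assumed 17-point benefit is exactly true.

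**The case against.** Several points on the other side stand.

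- **The endpoint is cumulative.** A new erosion at 6 months has already met it, so the outcome is known. A reader might infer that the second route should be deleted to match Protocol 11.1, or that erosions before randomisation should not count. The documents do not support that. Deletion would discard observed events and leave the third route, also event-only, in both documents. Erosions before randomisation also count for 12-month completers, because the window starts at enrolment; that is a matter of the endpoint, not of this rule.
- **SAP 8 already covers part of this.** Its complete-case analysis, restricted to patients with a known 12-month AMCE, removes the second route's effect, and the worst case triggers a tipping-point analysis. It would be wrong to say that the plan has no check. These are sensitivity analyses, however, and leave the primary rule as it is.
- **The effect is modest with equal missingness.** It is about one point, towards no difference, with type I error intact. The trial is double-blind and AMCE images are read by a blinded core laboratory, and nothing in the documents points to an imbalance.
- **The population wording can be read charitably.** SAP 6.1 names the mITT set specifically for this endpoint, and a 20% planning allowance can sit beside a hope of few missing data.
- **The list in SAP 4.1 is introduced as inclusive**, so it may not be exhaustive. But it gives no route for a 6-month-negative patient without a third exam.

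None of this restores the patients who are dropped.

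**Conclusion.** The concern holds in this form: without a 12-month AMCE, entry to the primary analysis requires a positive finding, and comparable patients with a clean 6-month exam are excluded. At the planned 20% loss, equal across arms, and an assumed 15% to 25% with 6-month erosions, the cost is 0.6 to 1.0 points of the 17-point difference and about 2 to 3 points of power. Bias away from a true null needs unequal missingness, which is an assumption here and could favour either strategy.

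A reader might go further and infer that the rule favours monotherapy or invalidates the primary test. The documents do not support either: equal missingness works against finding a difference, and they give no direction for any imbalance. This is a should-fix matter. The size is moderate, but the rule sits in the primary analysis and is cheap to mend.

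**What to change.** Make inclusion symmetric.

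1. Name one primary set in SAP 6.1, 8 and 9.2: all randomised patients (FAS).
2. Keep lesions observed at the 6-month or bleeding-driven exam as events, and align the wording of SAP 4.1 and Protocol 11.1.
3. For 6-month-negative patients without a third exam, multiply impute the 12-month result from arm, screening and 6-month AMCE findings, HP status and site.
4. Keep the complete-case analysis of 12-month completers as a sensitivity analysis.
5. Always run the tipping-point analysis, without making it conditional on the worst case.

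The cost is SAP wording and some programming; the exams are already scheduled. The downside is that the primary result would rest partly on an imputation model, which the complete-case and tipping-point analyses would help to test.

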### 4.2 Secondary variables

Secondary endpoints listed below will be evaluated.

1. The incidence and severity of gastric and intestinal mucosal lesions (a composite of erosion, ulceration or bleeding) during the first 6 months after study enrollment (prior to randomization);

2. The incidence and severity of gastric and intestinal mucosal lesions (a composite of erosion, ulceration or bleeding) within 6 months after randomization (between 6 months and 12 months after study enrollment);

3. The incidence of clinically evident gastrointestinal hemorrhage attributed to the upper GI tract (or of unknown origin) during 6 months after study enrollment (prior to randomization);

4. The incidence of clinically evident gastrointestinal hemorrhage attributed to the upper GI tract (or of unknown origin) after randomization (ie, between 6 months and 12 months after study enrollment);

5. The incidence of clinically evident gastrointestinal hemorrhage attributed to the upper GI tract (or of unknown origin) during 12 months after study enrollment;

6. Gastrointestinal symptoms within 6 months after enrollment, within 6 months after randomization, and within 12 months after enrollment (details in Protocol Appendix 3);

7. All bleeding (BARC types 1–5) events within 6 months after enrollment, within 6 months after randomization, and within 12 months after enrollment;

8. The incidence of target lesion failure (TLF; cardiac death, target-vessel MI, or clinically-driven target lesion revascularization), during the 12 months after enrollment;

9. The incidence of net adverse clinical events (NACE, defined as TLF or BARC type 2–5 bleeding) within 6 months after enrollment, within 6 months after randomization, and within 12 months after enrollment;

10. The incidence of stent thrombosis (Academic Research Consortium defined definite/probable) within 6 months after enrollment, within 6 months after randomization, and within 12 months after enrollment.

### **4.3 Safety variables**

Adverse events (AEs) of interest (i.e., abdominal distension, nausea, or vomiting after AMCE examination within 1 month) will be collected throughout the study period.

All serious adverse events (SAEs) will be recorded from the time of informed consent throughout the study.

Section 7 in the Protocol gives more detailed information on adverse event data collection.

## **5 Sample size**

The cumulative incidence of the primary endpoint of gastric or intestinal mucosal lesions within 12 months is estimated to be 47% in patients who received 12 months of DAPT and 30% in those treated with either aspirin or clopidogrel monotherapy beginning at 6 months after enrollment. With a 2:1 ratio in patients treated with either aspirin or clopidogrel monotherapy after 6-month DAPT versus DAPT for 12 months, 384 evaluable patients (256 and 128 respectively) provide 90% power to detect a 17% absolute risk reduction (36% relative risk reduction) with a 2-sided type I error of 0.05. Assuming 20% loss of evaluable primary endpoint outcome assessments due to patient withdrawal, loss to follow-up between 6 and 12 months or suboptimal AMCE visualization of the GI tract at 12 months, 480 patients are planned to be randomized. Assuming that an additional 10% of enrolled patients will not be randomized at 6 months because of adverse clinical events, noncompliance with antiplatelet therapy or lost to follow-up or withdrawal, 534 patients were initially planned to be enrolled after baseline screening. Finally, assuming that 10% of patients who undergo a screening AMCE examination will be excluded due to gastrointestinal ulcer or bleeding, approximately 593 patients were initially planned to be consented and undergo the screening AMCE examination.

## **6 Analysis sets**

### **6.1 Full analysis set (FAS)**

All patients who have been randomized to study treatment will be included irrespective of their protocol adherence and continued participation in the study. Patients will be analysed according to their randomized study drug assignment (not to which treatment they actually received) irrespective of whether the event occurred before or following discontinuation of study drug. Patients who withdraw consent to participate in the study (or are lost to follow-up) will be included up to the date of

their study termination except for vital status known through public records (for use in the analyses of deaths). All primary, secondary, and exploratory efficacy variables will be analyzed using the FAS. The primary endpoint of gastric or intestinal mucosal injury will be analyzed in a modified intention to treat (mITT) population, (i.e., patients with valid primary endpoint results). Unless otherwise stated, the FAS will be considered the primary analysis set for the primary and secondary variables and for the exploratory variables.

